## Abstract

**Background:**

Central sensitization has recently been documented in patients with knee osteoarthritis (OAk). So far, the presence of central sensitization has not been considered as a confounding factor in studies assessing the pain inhibitory effect of tens on osteoarthritis of the knee. The purpose of this study is to explore the pain inhibitory effect of burst tens in OAk patients and to explore the prognostic value of central sensitization on the pain inhibitory effect of tens in OAk patients.

**Methods:**

Patients with knee pain due to OAk will be recruited through advertisements in local media. Temporal summation, before and after a heterotopic noxious conditioning stimulation, will be measured. In addition, pain on a numeric rating score, WOMAC subscores for pain and function and global perceived effect will be assessed. Patients will be randomly allocated to one of two treatment groups (tens, sham tens). Follow-up measurements will be scheduled after a period of 6 and 12 weeks.

**Discussion:**

Tens influences pain through the electrical stimulation of low-threshold A-beta cutaneous fibers. The responsiveness of central pain-signaling neurons of centrally sensitized OAk patients may be augmented to the input of these electrical stimuli. This would encompass an adverse therapy effect of tens. To increase treatment effectiveness it might be interesting to identify a subgroup of symptomatic OAk patients, i.e., non-sensitized patients, who are likely to benefit from burst tens.

**Trial Registration:**

ClinicalTrials.gov: NCT01390285

## Background

Osteoarthritis (OA) is characterized by damaged articular cartilage of synovial joints. About 17% of people aged over 45 years suffer from pain and loss of function due to symptomatic knee osteoarthritis (OAk) [1] and 40% of people aged over 65 years have symptomatic OA of the knee or hip [2,3]. The prevalence of arthritis and more especially OA increases with age [4]. Therefore, the direct health care costs associated with this disease will become a major burden in the near future as the proportion of elderly people in the population increases [5]. Because there is no cure for OA, the treatment is focused on reducing physical disability and impairment and controlling pain while minimizing the potentially harmful side effects of medications [6].

### The use of transcutaneous electrical nerve stimulation (tens) in the management of OAk patients

Transcutaneous electrical nerve stimulation (tens) is a non-pharmacological, inexpensive and safe form of analgesia [7]. The pain modulating effect of tens is assigned to peripheral components which may be regulated by central mechanisms [8]. The inhibitory effect of tens is based on the 'Gate Control Theory' of pain perception as described by Melzack and Wall [9]. This theory suggests that stimulation of large (A-beta) afferent cutaneous fibers activate the inhibitory-interneurons in the dorsal horn of de medulla. This may weaken the transmission of nociceptive signals from small diameter A-delta and C-fibers. As OA is a dynamic process that involves phases of inflammation with possible increase of pain during these phases, tens may then be indicated as a facilitator for exercise. The use of tens to relieve knee pain in osteoarthritis of the knee (OAk) is recommended in various clinical guidelines as a conservative treatment to relieve knee pain [10-12]. However, Rutjes et al. [13] conclude in their meta-analysis that adequate evidence to support the use of any type of transcutaneous electrostimulation in patients with knee osteoarthritis is lacking.

### Central sensitization in patients with osteoarthritis of the knee

Central sensitization is defined as "an augmentation of responsiveness of central pain-signaling neurons to input from low-threshold mechanoreceptors" [14]. Central sensitization embodies modified sensory processing in the brain and malfunctioning of descending pain-inhibitory mechanisms [15]. The importance of central sensitization as a potential underlying mechanism of pain in OAk has recently gained interest [16]. In the past decade suggestions were already made concerning the influence of sensitization of wide dynamic range (WDR) dorsal horn neurons when explaining an increase of the mechanical pain threshold after applying a blockage of A -beta nerve fibers [17]. Continuous and intense nociceptive input from the OA-damaged knee joint may encourage central sensitization [18,19] and is assumed to play an important role in OA [20]. Central sensitization in patients with OAk was detected by Arendt-Nielsen and colleagues [16] by enhanced temporal summation (TS) of pain and impaired diffuse noxious inhibitory control (DNIC). TS is defined as an increase in pain rating after repetitive stimulation at a constant stimulus intensity [21]. It is thought to be a psychophysiological correlate of wind-up, which is defined as the increase in response magnitude of second-order nociceptive neurons and higher structures [22] to repetitive noxious stimulation [23]. DNIC is a phenomenon in which pain from one part of the body inhibits pain elsewhere in the body [21]. It appears that multireceptive WDR neurons in the dorsal horn of the spinal cord and trigeminal nociceptive play a key role in DNIC inhibitory processes [24]. These neurons are important convergence sites for both excitatory and inhibitory influences arising from more than one type of tissue and can be activated by both innocuous and noxious stimuli [25]. It has been suggested that DNIC functions as a filter, which allows the system to focus on a painful stimulus in a background of basic somesthetic activity. The mechanism appears to involve the spinal cord as well as supraspinal regions [25].

### Sensitization in relation to the effect of tens

The effectiveness of tens on knee pain in OAk patients is unclear, due to conflicting results [13]. The ambiguous results of the included studies could be due to the inclusion of heterogeneous types of patients. One important feature distinguishing patient groups might be the presence of central sensitization.

In case of central sensitization, the response to peripheral stimuli, e.g., electrical stimuli as well as mechanical pressure, cold, heat, light, sound and chemical substances is enhanced [26]. Tens (Burst) currents influence pain through the electrical stimulation of low-threshold A-beta cutaneous fibers. This stimulation might enhance the responsiveness of central pain-signaling neurons of OAk patients who are centrally sensitized. In these patients an adverse effect of tens on the pain perception can be expected. The identification of potential subgroups of sensitized and non-sensitized symptomatic OAk patients is needed, as they can react differently to tens. So far, the presence of central sensitization has not been considered as a confounding factor in studies assessing the pain inhibitory effect of burst tens on OAk.

### Aim of the proposed study

This study has a double aim. First to explore the pain inhibitory effect of burst tens in OAk patients. Second, to assess whether central sensitization affects this pain inhibitory effect. A 6 week burst tens intervention period will be succeeded by a 12 week follow up period. As an international consensus definition for central sensitization is lacking [26], we aim to assess the central sensitization by measuring pressure pain thresholds (PPT) at the knee (local pain) and at the upper limb (spreading pain) [27] and temporal summation before and during a heterotopic noxious conditioning stimulation [16,21]. The test-retest reliability of TS and DNIC has been reported as acceptable [21].

## Methods

### Study design

A randomized controlled clinical trial with blinded assessment and a follow-up period of 12 weeks is developed. This study will be conducted at the university hospital of the Vrije Universiteit Brussel (UZ Brussel), Brussels, Belgium. The research protocol is approved by the Medical Ethics Committee of the university hospital of the Vrije Universiteit Brussel (UZ Brussel). Written and signed informed consent will be obtained from all participants.

### Study population

A community sample of OAk patients with knee pain will be recruited.

### In- and exclusion criteria

To be included, patients need to be over 50 years old. All should have osteoarthritis in at least one knee fulfilling the American College of Rheumatology classification criteria [28] and report peak knee pain of more than 3 on a Numeric Rating Score (0-10 scale) over the last 24 hours.

Patients are excluded if they have had a knee surgery or intra-articular corticosteroid or hyaluronic acid injection [29] within 6 months, current or past (within 4 weeks) oral corticosteroid use, a history of knee joint replacement or tibial osteotomy, in case of contraindications to burst tens (pacemakers, epilepsy, dermatological conditions, abnormal sensation in the knees, pregnancy) or if they are unable to apply tens independently [7].

### Recruitment

Patients will be recruited through advertisements placed in local media. All patients will initially be screened over the phone with regard to selection criteria. If appropriate they will undergo medical screening with a project rheumatologist.

Consequently, an appointment for the baseline measurements will be made. Due to ethical considerations, analgesia and non-steroidal anti-inflammatory drugs will be permitted (and registered) as required and as participants are used taking during the last month. All participants will be asked to refrain from seeking other forms of treatment during the trial. They will be questioned about having received other forms of treatment in the final stage of the protocol.

### Randomization and blinding

Following baseline measurements, subjects will be randomly allocated to one of two treatment groups, ie., tens or sham tens. However, all patients will be told that two different kinds of tens are being tested. Randomization will be performed in blocks of four, stratified by sex and age. The allocation of this will be done by an independent researcher who will not interfere with other experimental procedures. We will use two boxes: one for each sex. In each box, subgroups will be made for five age categories: 50-59; 60-69; 70-79; 80-89; 90-99 years. Four numbered cards will be put in each age category. The numbering of the cards starts at one and ends at 40 and each number will correspond to a tens or a sham tens treatment. At the start of the study, each age category contains two tens and two sham tens treatments. Each time a new patient is included, a card will be taken out of the corresponding box and age category. When the four cards of one category are used, all of them will be put back in the box, so that a second round can be started. At each round, the numbered cards will be differently assigned to a tens/sham tens treatment by an independent researcher. The measurements will be carried out by a different researcher than the one that informs the patients concerning the treatment modalities. The information of the baseline measurements will remain concealed until the end of the study ensuring blinded assessment.

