### Interventions

The subjects that enter the tens -group will be asked to apply the tens therapy for at least 40 minutes continuously per day during 6 weeks. All patients in the intervention group will be informed that the intensity should be high enough so that an unpleasant but non-painfull sensation is acquired. The settings of the current will not change during the study. The patients that are assigned to the sham tens treatment will receive an inactive placebo tens therapy using a nonfunctional unit that appears to work but provides no stimulus. To blind the investigator as well as the patient, the sham tens device will deliver current for 30 seconds and then ramps down to no current. This approach has been studied and has been proven effective in blinding subjects and investigators to eliminate expectation bias [34]. All participants will be told that they may not feel anything after a while but that this does not mean that the machine is not working. All patients will be asked to come back after two and four weeks to assess their ability to precisely replicate the tens installation.

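### Fixed, published blocks of four within each sex-by-age stratum let anyone who learns the earlier arms know about 30% of allocations in advance; undisclosed mixed blocks cut this to about 6% at little cost (minor)

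*Protocol article*

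**What the plan says.** All of this is in the protocol article, Methods.

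- **Block size and strata** (Randomization and blinding): "Randomization will be performed in blocks of four, stratified by sex and age". The strata are physical: "We will use two boxes: one for each sex", and within each box "subgroups will be made for five age categories: 50-59; 60-69; 70-79; 80-89; 90-99 years".
- **Content of a block**: "At the start of the study, each age category contains two tens and two sham tens treatments". Cards go back only when all four in a category have been used.
- **Drawing**: "Each time a new patient is included, a card will be taken out of the corresponding box and age category".
- **Safeguards**: allocation follows the baseline measurements and is done by an independent researcher with no part in other procedures. Also, "At each round, the numbered cards will be differently assigned to a tens/sham tens treatment by an independent researcher".
- **Separation of roles**: "The measurements will be carried out by a different researcher than the one that informs the patients concerning the treatment modalities".
- **Instructions to patients** (Interventions): "All patients in the intervention group will be informed that the intensity should be high enough" to reach an unpleasant but not painful sensation. The sham device delivers current for 30 seconds and then none. The section states that this is meant to blind both patient and investigator.

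**The concern.** With a constant, published block of two plus two, knowing which arms have been used in the open block fixes what is left. The stratum depends only on sex and age, which are easily known at telephone screening, before the medical screening and the baseline appointment.

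Prediction needs knowledge of earlier arms, and the article leaves a plausible route to it. The intensity instruction is addressed to the active arm, so whoever gives it may well know the arm. That person is separated from the measurements, but the text does not separate them from screening or inclusion. Patients also return at two and four weeks to show that they can replicate the installation, and a nurse telephones weekly about handling the device. Active users feel continuing current and sham users do not.

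If a coming allocation can be foreseen, the decision to include a patient, or its timing, can depend on it. In a single-site trial with self-rated pain as the primary outcome, that is selection bias. It arises before allocation, so the planned intention-to-treat analysis cannot undo it.

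**Working it through.** **Reproducing the plan's own figure.** 2 sexes × 5 age bands × 4 cards = 40 cards, as the article states. The scheme is therefore ten strata with blocks of four.

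**Complete block of four, exact.** There are six equally likely orders of two tens (T) and two sham (S): TTSS, TSTS, TSST, STTS, STST, SSTT. The observer knows the earlier arms in the block.

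| Place in block | Probability that the next arm is certain | Probability that the best guess is right |
|---|---|---|
| 1 | 0 | 1/2 |
| 2 | 0 | 2/3 |
| 3 | 2/6 = 1/3 (after TT or SS) | 1/3 × 1 + 2/3 × 1/2 = 2/3 |
| 4 | 1 | 1 |

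- Certain: (0 + 0 + 1/3 + 1)/4 = 33.3%.
- Best guess right: (1/2 + 2/3 + 2/3 + 1)/4 = 70.8%.

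**120 patients over ten strata, by simulation.** The total of 120 is from the Sample size section. The mix of patients is not in the documents and is assumed: 65% women, with 28/38/25/8/1% in the five age bands. The observer knows every earlier allocation in the stratum. With mixed blocks, the observer also knows that sizes 4 and 6 are in use, but not which applies.

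| | Fixed 4 | 4 and 6 in random order |
|---|---|---|
| Certain allocations | 30.2% (0.302 × 120 ≈ 36) | 5.7% (0.057 × 120 ≈ 7) |
| Best guess right | 69.4% | 67.7% |
| Mean absolute difference between arms, overall | about 2.1 patients | about 2.3 patients |
| Absolute differences summed over strata | about 6.2 patients | about 6.8 patients |

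Repeat runs differ by about 0.1 in the imbalance figures. The fixed-block figure falls from 33% to 30% because last blocks are often unfinished.

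**Sensitivity to the assumed mix.** Three other age distributions (one similar, one uniform, one younger), all with 65% women, give 29.9% to 30.5% certain with fixed blocks and 5.6% to 5.8% with 4 and 6. Best-guess rates are 69.3% to 69.6% and 67.5% to 68.0%. The 33.3% does not depend on the mix.

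**Other sets of sizes.** Sizes 4/6/8 give 2.2% to 2.4% certain and a best-guess rate of about 66% to 67%. Sizes 2/4 give about 10% certain and do not lower the best-guess rate (about 71%).

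**The case against.** Three objections carry weight.

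1. **No documented leak.** A reader might infer that recruiting staff will foresee allocations. The article does not say so. No section describes a person who both knows earlier arms and controls inclusion, the sham is designed to blind the investigator, and the Equipment section speaks of teaching subjects to raise the intensity without limiting this to one arm. This stands: the 30% is conditional on knowing earlier arms, and only the plausibility of that knowledge can be argued.

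2. **The benefit depends on the measure.** A reader might infer that mixed blocks remove most predictability. They do not. The best guess is right almost as often (67.7% against 69.4%), and the share of places at which the observer can be at least 75% sure rises, from about 30% to 42% to 44%. A good guess can also influence inclusion. This stands too: the gain is confined to allocations known for certain.

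3. **Some suspicions go beyond the text.** One might suppose that the allocator and the person who re-maps the cards are the same and therefore know what each card means. The article does not say this, and the allocator has no part in other procedures anyway. Nor is re-mapping a weakness: it prevents decoding by card number across rounds, although it does nothing within an open block. Who holds the key and how the draw is concealed may be set out in a fuller protocol.

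What survives is that the fixed block size and its two-plus-two content are stated outright, so they are not details lost in condensation.

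**Conclusion.** The point holds as a minor one. The stated scheme makes 33% of places in complete blocks, or about 30% of 120 patients, certain to anyone who knows the earlier arms in the open block. Mixed blocks of 4 and 6 bring this to about 6%, a reduction of (30.2 − 5.7)/30.2 ≈ 81%. The best-guess rate falls by less than 2 percentage points.

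This rests on an assumed age and sex mix, to which the result is insensitive, and on an observer with full knowledge of earlier arms, which the documents make plausible but do not establish. The scheme contains no contradiction or wrong figure, and the documents do not support saying that allocation is compromised. The sample size is unaffected.

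**What to change.** Keep the sex and age strata, the independent researcher and the release of each allocation only after baseline. Replace the reusable cards with a list generated by computer before the first patient, with blocks of 4 and 6 in random order within each stratum. Do not disclose the sizes to anyone who screens, includes or instructs patients. Card re-mapping then falls away, since no card is reused.

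The cost is preparing one list, plus slightly more imbalance: about 0.2 patients overall (2.1 to 2.3) and about 0.6 summed over strata (6.2 to 6.8). The total of 120 does not change. Because mixed blocks do little against informed guessing, it would also help to state that whoever gives the intensity instruction takes no part in screening or inclusion.

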### Sample size

Sample size calculation is based on data from Law and Cheing [30]. They found a significant difference in the reduction of pain (2.9(4.7) points on a 0-10 VAS) when applying a tens current (pulse width: 200 μs, frequency: 100 Hz) on the knee of patients with OAk compared to a control group not receiving tens treatment. In this study the response within each subject group was normally distributed with standard deviation 4.7. If the true difference in the experimental and control means is 2.9, we will need to study 42 experimental subjects and 42 control subjects to be able to reject the null hypothesis that the population means of the experimental and control groups are equal with probability (power) 0.8. The Type I error probability associated with this test of this null hypothesis is 0.05. To take into account a 15% loss of data sample size is inflated up to 50 per group (n/0.85). Sample size is augmented by 10% per potential confounding factor (i.e. age and sex) [31]. The total sample size to be recruited will be 120 subjects.

### Baseline measurements

Age, gender, BMI, duration of knee OA symptoms, medication use, previous treatment and surgery for knee OA will be obtained at baseline.

#### Knee pain and physical function

Overall average knee pain (KPa) and peak pain intensity over the last 24 h (KPp) will be assessed by a 11-point numeric rating scale with terminal descriptors of 0 = no pain; 10 = maximal pain [32]. Self-reported knee pain and difficulty with physical function will be measured using the Western Ontario and McMaster Universities (WOMAC) Index [32].

#### Central sensitization

Temporal summation as well as diffuse noxious inhibitory control will be used to detect central sensitization. The assessment will be done in accordance with the protocol of Cathcart et al. [21]. The outcome assessor will be trained by an experienced researcher prior to the start of the study. The intra-observer reliability of the outcome assessor will be tested in a subgroup of the participants.

#### Pressure pain threshold (PPT)

Pressure stimuli will be measured using a hand held digital algometer (Somedic AB, Farsta, Sweden). Pain detection thresholds will be measured on the knee (M. Vastus Medialis) and on the upper part of the homolateral arm (lateral part of M. Deltoideus, 10 cm below acromion) [33]. The pressure will be increased at a rate of approximately 1 kg/s. Subjects have to report when the feeling of pressure alone changes into a feeling of pressure and pain (Pain Detection Threshold). The mean of two measurements, taken 30 s apart from each other, will be used for further use (temporal summation).

#### Temporal summation (TS)

Temporal summation assessment will start 2 min after PPT measurements to avoid contamination by possible sensitization from the pain threshold stimulation. TS will be induced at the knee and arm through 10 pressure pulses with the hand held algometer (Somedic AB, Farsta, Sweden) at PPT intensity. For each pulse, pressure will be increased at a rate of 2 kg/s and held during 1 s. An interstimulus interval of 1 s will be applied. Patients will be instructed to rate their pain level according to a NRS at the first, 5th and 10th pulse [21].

#### Diffuse noxious inhibition control (DNIC)

Ischemic compression of the heterolateral arm will be used as heterotopic noxious conditioning stimulation to evoke diffuse noxious inhibition control (DNIC). This method has previously been described [16,21]. A tourniquet cuff will be applied on the upper heterolateral arm and inflated until a painful intensity. After an adaptation period of 30 s, patients will be asked to rate the pain on a NRS. Cuff inflation will then be increased or decreased until a pain intensity of 3 of 10 on the NRS is reached. The arm is then rested while TS assessment is repeated as described above.

